#### Exclusion criteria

Patients presenting the following features will be excluded from the trial:
Pregnant women;Women who already presented UI before a stroke episode;Women who have a pacemaker implant;Women who use medication to treat NB; andWomen who have undergone medical treatment with botulinum toxin to treat NB.

### Who will take informed consent? {26a}

The signed informed consent form will be obtained from each patient prior to their participation in the study. The evaluator will acquire consent during the inclusion visit. The evaluator will explain all stages of the study, and the volunteers who agree to participate will sign the term.

### Additional consent provisions for the collection and use of participant data and biological specimens {26b}

Not applicable. There will be no biological sample collection in this study.

## Interventions

### Explanation for the choice of comparators {6b}

The techniques of TNES and PSES are noninvasive and widely used in clinical practice. No studies were found using this technique in women with NB after stroke. Therefore, we would such as to know which one is more effective for the treatment of poststroke women.

### Intervention description {11a}

The treatment of both groups will be performed twice a week for 6 weeks, totaling 12 sessions. The choice for the duration of treatment is based on previous studies that have shown the beneficial effects of neuromodulation caused by TNES after a mean treatment time of 12 sessions, twice a week. The present randomized controlled trial will be based on two sessions per week, given the belief that such treatment time would intensify the effects of electrostimulation on neuronal plasticity [11, 12].

Participants in the TNES group will be placed in the lateral decubitus position and the electrodes will be placed on the tibial region of the limb—counterlateral to the hemiplegic/hemiparetic side. One electrode will be placed posterior to the medial malleolus and another one will be placed approximately 10 cm above it (belly region of the posterior tibialis muscle). The participants in the PSES group will be positioned to achieve the greatest comfort. Two superficial electrodes will be placed on each side of S3 and S2 to directly stimulate spinal reflexes and reach suprasacral centers, as described in other studies [7] (Fig. 1).

**Fig. 1 Fig1:**
[figure not shown]
Images of electrode positions on the posterior tibial (**a**) and parasacral nerves (**b**)

Transcutaneous electrical nerve stimulation (TENS) was performed in the device model Neurodym Multibrand, IBRAMED®. Parameters applied to the TNES and PSES groups will be the same: wave frequency (F) at 10 Hz variation and pulse length (T) of 200 μs for 30 min [5, 12] (Fig. 2). This frequency was chosen because Jiang and Lindström [19] have shown that 10 Hz is the best frequency to cause bladder inhibition in mice. The current intensity in both groups will be increased according to the patients’ sensitivity limit.

**Fig. 2 Fig2:**
[figure not shown]
Protocol used in the Neurodym Multibrand device, IBRAMED®, in both groups

### Criteria for discontinuing or modifying allocated interventions {11b}

The criterion for discontinuation is the withdrawal of patient consent prior to publication of the results.

### Strategies to improve adherence to interventions {11c}

To improve adherence, telephone contact will be made with the volunteers the day before the intervention session to remind them of their appointment.

### Relevant concomitant care permitted or prohibited during the trial {11d}

During the protocol, medical consultations and the intake of medications are allowed, with the exception of medication for the treatment of NB.

### Provisions for posttrial care {30}

Researchers are responsible for any harm that occurs as a result of the study. Thus, the researchers will provide for participants’ health care needs that arise as a direct consequence of trial participation.

### Outcomes {12}

#### Primary outcome measure

The primary outcome measure is any changes in the International Consultation on Incontinence Questionnaire-Short Form (ICIQ-SF) from baseline to final evaluation. The ICIQ-SF questionnaire is simple and fast (only four questions), and it will be used for UI impact evaluation. This questionnaire has general scoring ranging from 0 to 21 points; the closer to 21 points the score is, the stronger the impact of urinary losses on quality of life [11, 20].

#### Secondary outcome measures

The secondary outcomes of the study are urinary frequency during the day and night, number of incontinence episodes, and quality of life. A bladder diary was used to assess urinary habits in order to quantify daytime and nocturnal urination frequency and episodes of incontinence. Volunteers will be oriented to fulfill a table with this information, provided by the researchers, for 3 days [21].

The World Health Organization Quality of Life – BREF (WHOQOL-BREF) questionnaire will be used to assess the quality of life before and after the intervention. This instrument was developed by the World Health Organization and is based on the quality of life concept, which encompasses positive (medication mobility, played role, satisfaction) and negative points (fatigue, pain, medication dependence, and negative feelings) [22]. The questionnaire comprises 26 questions with 5 coordinated options. There are 24 questions in the four domains (physical, psychological, social relationships, and environment) composing the original instrument and two general questions regarding the quality of life [23, 24]. Each specific domain is assessed based on values found through the WHOQOL-BREF—the higher the score is (maximum = 100), the better the quality of life related to that domain [25].

### Participant timeline {13}

All assessments will be carried out at baseline and after 12 intervention sessions. The schematic diagram of the participant timeline can be seen in Fig. 3.

**Fig. 3 Fig3:**
[figure not shown]
Flow diagram of the trial design

### Sample size {14}

Studies that applied the techniques to other populations were analyzed to estimate the percentage of improvement in urinary symptoms after application of TNES and PSES. The studies of Malm-Buatsi et al. [26], Monteiro et al. [15], and Kabay et al. [27] were analyzed. Thus, considering a confidence of 99%, a power of the test of 90%, considering the proportion of patients who had improvement after TNES of 69% (PA = 0.69) and patients who had improvement after PSES of 13% (PB = 0.13), the sample size for each group was 22 women. To calculate the sample, Bioestat 5.0 software was used [28].

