### Plans to promote participant retention and complete follow-up {18b}

Intention-to-treat analysis will be carried out [31]. Therefore, all participants who discontinue or deviate from the initially randomized intervention will be evaluated. Those participants who discontinue the intervention will receive telephone contact from the researcher after 6 weeks of the first evaluation to attend the laboratory for reevaluation.

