## Statistical methods

### Statistical methods for primary and secondary outcomes {20a}

Statistical Package for the Social Sciences (SPSS Statistics version 23) software will be used in the statistical analysis. The Shapiro-Wilk test will be initially applied to assess data normality. Data will be described as the mean (standardized deviation) for normally distributed continuous variables, median (interquartile range) for continuous variables without normal distribution, and frequency (percentage) for categorical variables.

For parametric data, comparison between the groups will be carried out using the analysis of variance (ANOVA) test. Significance values lower than 0.05, at the 95% confidence interval, will be interpreted as statistically significant. The clinical relevance of recorded values will be confirmed through effect-size calculations (Cohen’s *d*) based on significant differences. The following effects will be taken into account: 0.00 to 0.49, low; 0.50 to 0.79, medium; and above 0.80, high [32]. The intention-to-treat analysis will be carried out [31].

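### The stated 90% power belongs to a responder comparison at the 1% level, not to the planned ANOVA of ICIQ-SF change at the 5% level

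*Protocol article*

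**What the plan says.** All places are in the Protocol article.

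- **Sample size {14}** works from proportions of patients improved, taken from studies in other populations. It reads "considering a confidence of 99%, a power of the test of 90%, considering the proportion of patients who had improvement after TNES of 69" percent. The other rate is given as "patients who had improvement after PSES of 13% (PB = 0.13"), and the result is 22 women per group, 44 in all.
- **Primary outcome measure** is a score: "The primary outcome measure is any changes in the International Consultation on Incontinence Questionnaire-Short Form (ICIQ-SF) from baseline to final evaluation". The scale runs from 0 to 21. No cut-off defines an improved patient.
- **Statistical methods {20a}** plans ANOVA between groups for parametric data, with Cohen's *d* as the effect size. The level is given as: "Significance values lower than 0.05, at the 95% confidence interval, will be interpreted as statistically significant".
- **Objectives {7}** expects improvement in both groups and no difference between them.

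**The concern.** Three things differ between the calculation and the analysis: the endpoint (patient improved or not, against a score), the test (two proportions, against ANOVA of a continuous measure) and the significance level (1% against 5%). The article says nothing to connect them. It is also not a detail left to a fuller document, because the article makes a specific power claim and names a specific primary outcome and test, and these do not match.

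What is at stake is how a non-significant result will be read. The investigators expect no difference between the techniques. If that is what they find, the 90% figure will sit beside it and invite the conclusion that the primary comparison was well placed to detect a difference. Nothing in the article shows for which difference in ICIQ-SF that would be true.

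**Working it through.** **Step 1. Reproduce the 22.** Inputs from the sample size section: p₁ = 0.69, p₂ = 0.13, difference 0.56, mean proportion 0.41, power 90% (z = 1.2816), 1:1 allocation. Sidedness is not stated.

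Uncorrected formula: n = [z_α √(2 × 0.41 × 0.59) + z_β √(0.69 × 0.31 + 0.13 × 0.87)]² / 0.56²

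The square roots are 0.6956 and 0.5718. At two-sided 1% (z_α = 2.5758):

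n = (1.7916 + 0.7328)² / 0.3136 = 20.3

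Continuity correction: n_c = (n/4) × [1 + √(1 + 4/(0.56 n))]²

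| Level | Sides | Uncorrected n | Corrected n |
|---|---|---|---|
| 1% | two | 20.3 | 23.8 |
| 1% | one | 17.6 | 21.04, rounding up to 22 |
| 5% | two | 14.0 | 17.4 |
| 5% | one | 11.2 | 14.6 |

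The stated 22 fits a two-proportion design at 1% and does not fit at 5%. So the 99% was really used and is not a slip for 95%.

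**Step 2. Effect of the level alone.** For 69% against 13% with 22 per arm, exact power of the two-sided chi-square test is 93% at 1% and 98% at 5%. For the binary test, sizing at 1% and testing at 5% is therefore conservative. The problem comes from the change of endpoint.

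**Step 3. Power of the planned type of analysis.** With two groups, ANOVA of the change scores is equivalent to a two-sided *t* test. With 22 analysed per arm there are 42 degrees of freedom, the 5% critical value is 2.018, and the noncentrality is d × √(22/2) = 3.317 d, where d is the difference in mean change divided by the SD of change. The article gives neither a difference nor an SD, so d is an assumed range.

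| d (SD of change) | Power, 22 per arm |
|---|---|
| 0.5 | 37% |
| 0.8 | 74% |
| 0.865 | 80% |
| 1.00 | 90% |

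The article's own bands for Cohen's *d* call 0.50 to 0.79 medium and values above 0.80 high.

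**Step 4. Fewer women analysed.** The article states no loss rate. If 18 per arm were analysed (an assumption: 4/22 = 18% lost), 80% power would need d = 0.96 and 90% would need d = 1.11.

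**The case against.** **The assumed effect is very large on any scale.** If improvement were a cut on a normally distributed change score, 69% against 13% would correspond to d = 0.496 + 1.126 = 1.62. At d of about 1.6 the planned test has over 99% power with 22 per arm. On that reading the trial has more power than stated for the effect it assumed, and a reader of a 56-point difference would not expect power for moderate effects. This stands, and it blocks the inference that the trial is underpowered. It does not rescue the power statement: the article defines no such cut and gives no translation to ICIQ-SF, the rates come from other populations, and the objectives expect no difference.

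**The level mismatch favours the trial.** This stands for the binary test, as step 2 shows. It should be reported as an inconsistency, not as a loss of power.

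**Loss of participants.** A reader might infer that the plan expects dropout and failed to allow for it. The text does not support that. The retention section says that "all participants who discontinue or deviate from the initially randomized intervention will be evaluated", with a recall by telephone, and the missing-data section only says what will be described if data are missing. Stopping treatment is not the same as losing the outcome. Any figure for 18 per arm is illustrative.

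**The ANOVA model is not spelled out.** Baseline adjustment would help. At an assumed baseline-to-final correlation of 0.5 (where the SD of change equals the SD of the score), 90% power needs about 1.0 × √(1 − 0.5²) = 0.87 SD. Any reading still compares a score and not a proportion.

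**Conclusion.** The point holds as an inconsistency, not as an arithmetic error. The 22 is right for its own inputs, but the 90% power is a property of a responder comparison that the trial does not plan to make. For the analysis that is planned, 22 analysed per arm gives 90% power at about 1.0 SD of change, 80% at 0.87 SD and 37% at 0.5 SD, assuming a two-sided 5% test, equal SDs and all 44 women analysed.

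A reader might go on to infer that the trial is too small. The documents do not support that, because they give no target ICIQ-SF difference and no SD, and the d values above are assumptions. What can be said is narrower: a null result, which the objectives predict, cannot be presented as backed by 90% power except against a difference of about 1 SD.

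**What to change.** Keep 44 women and change wording only.

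1. Add to the sample size section: *With 22 analysed per arm, a two-sided 5% comparison of mean change in ICIQ-SF has 90% power for a difference of 1.0 SD of change and 80% for 0.87 SD (37% at 0.5 SD).*
2. Keep the 69%/13% calculation at 99% confidence as the historical basis of the sample size, since recruitment began in January 2019 on that basis. Label it as a responder calculation that does not give the power of the primary analysis.
3. State there that the analysis uses the 5% level.
4. If a figure for fewer women is given (for example 0.96 and 1.11 SD for 80% and 90% power with 18 per arm), label the loss as assumed.

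The cost is a less favourable power statement. No extra patients are needed. The added sentence does not turn a non-significant difference into evidence that the two techniques are equivalent, and the report should not use it that way.

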### Recruitment {15}

Volunteers from the community in Uberlândia, Brazil, will be recruited for the trial after information about the research is publicized. The recruitment information will be carried in newspaper and radio announcements, e-mails, social networks, and visitations to the rehabilitation center in the city.

## Assignment of interventions: allocation

### Sequence generation {16a}

Participants will be randomized in a 1:1 ratio to the TPES or PSES group by computer-generated random numbers.

### Concealment mechanism {16b}

A researcher not involved in the data collection will assign the groups by the sealed envelope method. The opaque envelopes will be numbered and kept locked away, available only to the study researchers.

### Implementation {16c}

After including the participant, the researcher responsible for the interventions will open the envelope with the lowest number available to determine which group the participant belongs to.

## Assignment of interventions: blinding

### Who will be blinded? {17a}

The researcher in charge of the interventions to be applied to the patients will be blind to the assessments. The researcher in charge of the initial and final evaluations and the one accounting for data processing will be blind for treatment allocation. Patients will not be blind to the procedure because of the difficulties set by differences between techniques.

### Procedure for unblinding if needed {17b}

The loss of blinding should not be carried out unless there is a threat to the participant’s safety as a consequence of the study procedures.

## Data collection and management

### Plans for assessment and collection of outcomes {18a}

A trained researcher will perform all assessments at baseline and after 12 sessions. The Portuguese version of the ICIQ questionnaire presents satisfactory reliability and construct validity [20], which is a questionnaire widely used in research and clinical practice because it is robust, brief, and simple [29].

The 3-day bladder diary was chosen because its reliability is efficient regarding the number of micturition episodes per day and episodes of urgency in patients suffering from neurogenic urinary dysfunction [30].

Fleck et al. [23] demonstrated that the Portuguese version of the WHOQOL-BREF showed a good performance concerning internal consistency, discriminant validity, criterion validity, concurrent validity, and test-retest reliability. Therefore, this questionnaire allies good psychometric performance and practicality for use.

### Plans to promote participant retention and complete follow-up {18b}

Intention-to-treat analysis will be carried out [31]. Therefore, all participants who discontinue or deviate from the initially randomized intervention will be evaluated. Those participants who discontinue the intervention will receive telephone contact from the researcher after 6 weeks of the first evaluation to attend the laboratory for reevaluation.

### Data management {19}

Following the institution’s protocols, all data will be considered anonymous, and participants will be identified by numbers. All source documents will be stored in locked file cabinets with secure and limited access. The data will be transferred to a secure online data cloud through double-checking between researchers. Only the research group has an individual password to access the data.

### Confidentiality {27}

The study will be conducted in accordance with Brazilian rules and regulations. All data generated in this study will remain confidential. Only the research team has access to the study data. Access to data will only be provided in the event of audits or regulatory regulation by the institution.

### Plans for collection, laboratory evaluation, and storage of biological specimens for genetic or molecular analysis in this trial/future use {33}

Not applicable as no biological samples will be collected.

## Statistical methods

### Statistical methods for primary and secondary outcomes {20a}

Statistical Package for the Social Sciences (SPSS Statistics version 23) software will be used in the statistical analysis. The Shapiro-Wilk test will be initially applied to assess data normality. Data will be described as the mean (standardized deviation) for normally distributed continuous variables, median (interquartile range) for continuous variables without normal distribution, and frequency (percentage) for categorical variables.

For parametric data, comparison between the groups will be carried out using the analysis of variance (ANOVA) test. Significance values lower than 0.05, at the 95% confidence interval, will be interpreted as statistically significant. The clinical relevance of recorded values will be confirmed through effect-size calculations (Cohen’s *d*) based on significant differences. The following effects will be taken into account: 0.00 to 0.49, low; 0.50 to 0.79, medium; and above 0.80, high [32]. The intention-to-treat analysis will be carried out [31].

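### The between-group test, including the one for the primary outcome, hangs on a normality pre-test of the outcome data, and no comparison is given for outcomes that fail it

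*Protocol article*

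**What the plan says.** Section {20a} of the protocol article opens the analysis with "The Shapiro-Wilk test will be initially applied to assess data normality". Description follows: mean and SD for normally distributed variables, and "median (interquartile range) for continuous variables without normal distribution". The comparison is then given in one sentence: "For parametric data, comparison between the groups will be carried out using the analysis of variance (ANOVA) test". No covariate is named. No rank test, transformation or count model appears there, or in the sections on interim analyses, additional analyses and missing data. The significance level is 0.05, and the only effect measure is "effect-size calculations (Cohen’s *d*) based on significant differences".

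The primary outcome is "any changes in the International Consultation on Incontinence Questionnaire-Short Form (ICIQ-SF) from baseline to final evaluation". On its scale: "This questionnaire has general scoring ranging from 0 to 21 points". Among the secondary outcomes, a 3-day bladder diary is used "to quantify daytime and nocturnal urination frequency and episodes of incontinence". Eligibility requires overactive bladder after stroke. The Background defines overactive neurogenic bladder as occurring with or without incontinence, so women with no leakage can enter.

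**The concern.** A rule that looks at the outcome data before choosing the test leaves the primary analysis open until those data are seen. Here only one side of the rule is filled in. It also leaves room for choice: the article does not say whether normality is judged per arm or pooled, on raw values or on changes, or at what level.

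This bears on the trial's own aim. The Objectives section expects no difference between the groups. Such a result can be read only through an estimate with its confidence interval, produced the same way whatever the data look like. Under the stated plan the effect size is mean-based and tied to significant differences, and the method could differ from one outcome to the next.

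**Working it through.** **Reading.** Three statements of {20a} stand in sequence: a normality test comes first; non-normal variables get a median and interquartile range; ANOVA applies to parametric data. The third is conditional, and the only instrument in the section that could settle the condition is the first. The non-normal branch ends at description.

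**Number per arm.** The plan's 22 per group sets the size at which the pre-test runs. With p1 = 0.69, p2 = 0.13, two-sided alpha 0.01 and power 0.90:

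n = [2.576·√(2·0.41·0.59) + 1.282·√(0.69·0.31 + 0.13·0.87)]² / 0.56² = (1.792 + 0.733)² / 0.3136 ≈ 20.3, so 21.

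A one-sided calculation with continuity correction gives exactly 22. The stated figure is reproduced closely enough, and 22 is used below.

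**How often Shapiro-Wilk rejects.** The article gives no mean, SD or dispersion for any outcome, so all distributions here are assumptions. With p the simulated rejection rate at 0.05 in one arm of 22, the chance of rejection in at least one of two arms is 1 − (1 − p)².

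| Assumed 3-day count | p, one arm | At least one arm |
|---|---|---|
| Negative binomial, k = 1, mean 3 / 6 / 9 | 0.952 / 0.908 / 0.893 | 99.8% / 99.2% / 98.9% |
| Negative binomial, k = 2, mean 3 / 6 / 9 | 0.783 / 0.645 / 0.601 | 95% / 87% / 84% |
| Negative binomial, k = 5, mean 3 / 6 / 9 | 0.522 / 0.345 / 0.312 | 77% / 57% / 53% |
| Poisson, mean 6 / 9 / 15 | 0.170 / 0.121 / 0.087 | 31% / 23% / 17% |
| Truly normal | 0.051 | 10% |

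For example, at k = 2 and mean 9: 1 − (1 − 0.601)² = 0.841. Poisson counts with a mean of 30 are rejected in at least one arm in about 12% of trials. Repeat simulations at k = 5 and mean 6–9 gave 51–57%.

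**Primary outcome (ICIQ-SF change).** Assume baseline mean 12 and SD 4.5, whole-point scores held within 0–21, a mean fall of 3 to 6 points and an SD of the fall of 2 to 5. Rejection in at least one arm is then about 10–32%. The upper end arises when the SD of the fall is small and the change takes few distinct values.

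Women who score zero at both visits raise the rate. In a second set-up (baseline mean 14, SD 4; final mean 8, SD 5; correlation 0.5), with 20% of women at zero both times, p = 0.3625 and 1 − 0.6375² = 59%. With 30%, p = 0.662 and 1 − 0.338² = 89%.

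**The case against.** **The gate is partly inferred.** The sentence after the Shapiro-Wilk statement concerns descriptive summaries, and the article nowhere says that its p-value switches the test. This stands as a caveat. Still, ANOVA is expressly limited to parametric data, and nothing else in the section defines what counts as parametric.

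**The fallback may sit in a fuller plan.** A condensed article need not name every alternative test, so the unnamed test alone would not be a finding. What remains is a rule the article does state: the method depends on the outcome data. Naming a rank test would fill the gap but keep the dependence.

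**Stronger readings.** A reader might infer that the primary score is bound to fail because it is bounded and piles up at zero. The documents do not support this. The primary is the change, not the final score. With a mean fall of 6, the final score is rejected in at least one arm in roughly 37–78% of trials, but the change in only about 14–30%.

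A reader might also infer that diary counts fail almost always. That needs strong overdispersion or many zeros; near-Poisson counts mostly pass.

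Nor would a substituted rank test discard a baseline adjustment, since the plan states none. It need not lack an estimate either, because a Hodges-Lehmann shift with its interval is in points or episodes. Finally, a failure rate of about 19% for normal data (1 − 0.95⁴) presumes four independent tests, by arm and visit, which the article does not describe.

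**Conclusion.** The concern holds in a limited form. On the natural reading of {20a}, a normality test of the outcome data decides whether an outcome receives the only comparison stated, an ANOVA without covariates, and outcomes that fail have none. For leakage counts the empty branch would be reached in anything from about 12% to nearly all trials, depending on an overdispersion the article does not give. Entry without required leakage makes excess zeros plausible. For the primary, about 10–32% under the assumed falls and SDs is a material chance but not a likely outcome, unless about 20% or more of women score zero at both visits.

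The case for change does not rest on these percentages. Baseline and final values are collected anyway, so one fixed, baseline-adjusted model is available at no extra burden to participants and is a better method than a conditional, unadjusted ANOVA. The sample size is not affected.

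**What to change.** State in {20a} that normality checks serve only to choose descriptive summaries and do not select the test. Then fix the following in advance:

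- **Primary:** ANCOVA of final ICIQ-SF on group, adjusted for baseline ICIQ-SF, whatever the distribution looks like. Report the adjusted mean difference with its 95% CI, whether or not it is significant. Add a robust-standard-error or permutation check as sensitivity analysis.
- **WHOQOL-BREF domains:** the same model, with each domain's baseline value as covariate.
- **Diary counts (day and night voids, incontinence episodes):** one named, baseline-adjusted method suited to counts. Negative binomial regression is one option; ANCOVA with a robust or bootstrap interval is another. At 22 per arm the choice is partly preference; what matters is that it is made before the data are seen.

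The cost is a few sentences and a little more analysis work, with no new data and no more participants. The Trial status section reports recruitment still incomplete, and the article describes an amendment route through the ethics committee and the registry.

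### The group comparison is an ANOVA of unstated form with no baseline ICIQ-SF covariate; a baseline-adjusted ANCOVA would be more precise at almost no cost

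*Protocol article*

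**What the plan says.** All of this is in the protocol article.

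- Primary outcome measure: "The primary outcome measure is any changes in the International Consultation on Incontinence Questionnaire-Short Form (ICIQ-SF) from baseline to final evaluation".
- Participant timeline {13}: "All assessments will be carried out at baseline and after 12 intervention sessions". Every woman who attends both visits therefore has a baseline and a final ICIQ-SF score.
- Statistical methods {20a}: "For parametric data, comparison between the groups will be carried out using the analysis of variance (ANOVA) test". No covariate is named, and neither is the score or model term that the ANOVA tests. The threshold follows: "Significance values lower than 0.05, at the 95% confidence interval, will be interpreted as statistically significant".
- Sample size {14}: 22 women per group, from a comparison of two improvement proportions (0.69 and 0.13), "considering a confidence of 99%, a power of the test of 90" percent.
- Objectives {7}: the stated hypothesis is that both groups improve and do not differ from each other.

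**The concern.** When an outcome is measured before and after treatment, the baseline value usually explains part of the spread in the final value. An analysis that uses baseline as a covariate removes that part. A plain ANOVA of final scores removes none of it, and an ANOVA of change scores removes it with a fixed coefficient of 1, which is generally not the best one.

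Two things are at stake in a trial of 44 women. The first is power and the width of the confidence interval. The second is exposure to chance imbalance in baseline severity. Precision matters more than usual here because the authors expect no difference between groups: a non-significant result from a noisy comparison could be read as support for that expectation.

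The form of the ANOVA is also open. The outcome definition points to change scores, but the analysis sentence does not say so, and the three candidate forms do not all have the same precision.

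**Working it through.** **The plan's own figure.** With p1 = 0.69, p2 = 0.13, alpha 0.01 and power 0.90, the mean proportion is 0.41 and the difference 0.56. Two-sided, without continuity correction:

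n = [2.576·√(2·0.41·0.59) + 1.282·√(0.69·0.31 + 0.13·0.87)]² / 0.56² = 20.3, so 21 per group.

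The continuity correction gives 24 two-sided and 22 one-sided. The stated 22 is thus reproduced to within two women. It concerns a binary improvement endpoint at alpha 0.01, so it gives no power for the ICIQ-SF comparison.

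**Inputs for the comparison of methods.** From the article: 22 per arm, significance level 0.05, ICIQ-SF at two visits. Assumed: a two-sided test (sidedness is not stated), equal variances at the two visits, a baseline-final correlation r between 0.3 and 0.8, and a true difference of 0.5 or 0.8 SD of the final score. The article gives no ICIQ-SF standard deviation, target difference or correlation.

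**Variance of the group contrast, in units of the final-score variance.**

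- ANOVA of final scores: 1.
- ANOVA of change scores: 2(1 − r). With two visits, the group-by-time test is the same test.
- ANCOVA: 1 − r².

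Relative to change scores, ANCOVA's variance is (1 − r²)/[2(1 − r)] = (1 + r)/2. The degree of freedom spent on the covariate multiplies the ANCOVA variance by about 1 + 1/40 = 1.025. That factor is in the power columns but not in the variance columns.

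| r | Change | ANCOVA | Cut vs change | Cut vs final | Power at 0.8 SD: final / change / ANCOVA | Power at 0.5 SD: final / change / ANCOVA |
|---|---|---|---|---|---|---|
| 0.3 | 1.40 | 0.91 | 35% | 9% | 74 / 59 / 76% | 37 / 28 / 39% |
| 0.5 | 1.00 | 0.75 | 25% | 25% | 74 / 74 / 84% | 37 / 37 / 46% |
| 0.7 | 0.60 | 0.51 | 15% | 49% | 74 / 92 / 95% | 37 / 55 / 61% |
| 0.8 | 0.40 | 0.36 | 10% | 64% | 74 / 98 / 99% | 37 / 73 / 76% |

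Power comes from the noncentral F distribution with 22 per arm. The noncentrality is (d·√(22/2))² divided by the relative variance.

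**The same gain in women.** Before the small-sample factor, ANCOVA on 44 women is worth 44·2/(1 + r) women under change-score ANOVA: about 68, 59, 52 and 49 for r = 0.3, 0.5, 0.7 and 0.8. Against final-score ANOVA it is worth 44/(1 − r²): about 48, 59, 86 and 122.

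**Chance imbalance.** The standard error of the baseline difference is √(2/22) = 0.30 SD, so an imbalance beyond 0.3 SD in either direction arises in roughly one trial in three. If the baseline difference is D, a final-score ANOVA carries r·D into the estimate. A change-score ANOVA carries r·D − D = −(1 − r)·D, which over-corrects. At r = 0.5 and D = 0.3 SD these are +0.15 and −0.15 SD. ANCOVA removes the imbalance in expectation.

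**The case against.** The strongest reply is that nothing here is invalid. In a randomised trial, unadjusted comparisons of final or change scores are unbiased and hold their type I error, so this is a matter of efficiency. That stands.

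Several stronger readings are tempting, and the article does not support them.

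- *The plan ignores baseline.* The primary outcome is defined as "any changes in the International Consultation on Incontinence Questionnaire-Short Form (ICIQ-SF) from baseline to final evaluation". On the natural reading, baseline is subtracted; it is only not used as a covariate.
- *Chance imbalance is left uncorrected.* That would be true of final scores. Change scores over-correct it instead.
- *The group main effect of a two-way ANOVA will be read as the treatment effect.* That term would average in the pre-treatment score and dilute the effect, but the article names no two-way model and no such reading of it. With an outcome defined as change, group-by-time would be the relevant term.
- *The planned 90% power is broken.* That figure belongs to a different endpoint and alpha, and the article states no power for ICIQ-SF.

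It can also be said that a condensed article may leave covariates to a fuller plan, and that the entry under additional analyses, where none are planned, concerns matters such as subgroups and does not rule out a covariate in the main model. Both are fair. But the article does commit to a named method, and whichever form is meant, adding baseline as a covariate improves on it at any material correlation.

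Finally, the gain depends on r. Against change scores it is small at high r (73% against 76% power for 0.5 SD at r = 0.8). Against final scores it is small at low r. This also stands, and is why a range is shown.

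**Conclusion.** The point holds as a worthwhile and nearly free improvement to a valid analysis. The article names an ANOVA without a baseline covariate and does not fix its form. Under the change-score reading that the outcome definition favours, ANCOVA would reduce the variance by between about 10% (r = 0.8) and 35% (r = 0.3). If final scores were meant, the range is 9% (r = 0.3) to 64% (r = 0.8). The small-sample factor takes back about 2.5% of the ANCOVA variance.

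That ANCOVA is at least as good as either form at material correlations follows from the formulas under equal variances. The size of the gain does not follow from the article: it rests on the assumed correlation and, for power, on the assumed difference.

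**What to change.** State in the statistical methods section that the primary analysis is an ANCOVA of final ICIQ-SF on allocated group, with baseline ICIQ-SF as covariate, reporting the adjusted mean difference with its 95% CI and p-value. Reporting these whether or not the result is significant also serves the stated expectation of no difference better than an effect size given only after a significant test. The existing restriction to parametric data can stay, applied to the model residuals.

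For secondary outcomes, use the same form with each outcome's own baseline where a normal-error model is suitable, such as the WHOQOL-BREF domains. For the bladder-diary episodes, use a baseline-adjusted model suited to counts; a normal-error ANCOVA should not be imposed on every outcome.

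The cost is a short text change and one degree of freedom, with no new data or visits, in standard software. Recruitment began in January 2019. If the change counts as a major modification, the article's own rule requires a formal amendment, ethics approval and a registry update. It should be made before outcomes are compared by group.
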